# The effects of combined motor control and isolated extensor strengthening versus general exercise on paraspinal muscle morphology and function in patients with chronic low back pain: a randomised controlled trial protocol

**DOI:** 10.1186/s12891-021-04346-x

**Published:** 2021-05-22

**Keywords:** Low back pain, Motor control, Multifidus, MRI, Ultrasound

## Abstract

**Background:**

Exercise is a common approach for the management of patients with chronic non-specific low back pain (LBP). However, there is no clear mechanistic evidence or consensus on what type of exercise is more effective than others. While considerable evidence suggests a link between lumbar muscle health (e.g., atrophy and fatty infiltration) with functional deficits, it is unknown whether exercises targeting the lumbar spine can lead to noticeable improvements in muscle health and functional outcomes. The primary aim of this study is to compare the effect of combined motor control and isolated strengthening lumbar exercises (MC + ILEX) versus a general exercise group (GE) on multifidus muscle morphology (size and composition). Secondary aims include assessing the effect of the interventions on overall paraspinal muscle health, pain and disability, as well as psychological factors as possible effect modifiers.

**Methods:**

A total of 50 participants with chronic non-specific LBP and moderate to severe disability, aged between 18 and 60, will be recruited from the local orthopaedic clinics and university community. Participants will be randomised (1:1) to either the MC + ILEX or GE group. Participants will undergo 24 individually supervised exercise sessions over a 12-week period. The primary outcome will be multifidus morphology (atrophy) and composition (fatty infiltration). Secondary outcomes will be muscle function (e.g., % thickness change during contraction), morphology, lumbar extension strength, pain intensity and disability. Potential treatment effect modifiers including maladaptive cognitions (fear of movement, catastrophizing), anxiety, depression, physical activity, and sleep quality will also be assessed. All measurements will be obtained at baseline, 6-week and 12-week; self-reported outcomes will also be collected at 24-week. Between-subjects repeated measure analysis of variance will be used to examine the changes in paraspinal muscle morphology over the different time points. Linear mixed models will be used to assess whether baseline scores can modify the response to the exercise therapy treatment.

**Discussion:**

The results of this study will help clarify which of these two common interventions promote better results in terms of overall paraspinal muscle heath, back pain, disability and psychological factors in adults with chronic LBP.

**Trial registration:**

NTCT04257253, registered prospectively on February 5, 2020.

## Background

Low back pain (LBP) is one of the leading causes of disability worldwide [1, 2], costing billions of dollars in Canada alone each year, including health care costs and missed work [3]. While chronic LBP is a prevalent and persistent global burden, up to 90% of the North American population alone, is at risk of developing LBP [3–5]. Of these cases, only 10% are thought to be the result of identifiable radiological characteristics, such as nerve root compression, fractures, or stenosis [6]. The remaining cases are classified as non-specific LBP, which unsurprisingly, present with a variety of clinical manifestations without diagnostic or therapeutic options. LBP is significantly associated with high levels of disability, decreased function and participation in life as well as decreased sleep quality and increased depressive symptoms [7–9]. Currently, exercise therapy is the most common conservative treatment for LBP as it is easily accessible and can be individually tailored to patient’s needs [10]. Exercise has been bound to improve pain, quality of life and psychosocial aspects of pain such as pain-related fear (catastrophizing), kinesiophobia, depression, and anxiety [11–13]. Although exercise is more effective than no intervention, the effect size of exercise are small to moderate, and to date there is no evidence that one exercise approach is superior to another [14–16].

Individuals with LBP are more likely to have muscle atrophy, fatty infiltration, and asymmetries of the lumbar musculature, specifically the multifidus muscle [17–19]. Possible mechanisms for degenerative muscle changes include poor motor control, decreased muscle activation, and fatigue. Loss of motor coordination can lead to repetitive mechanical stress on surrounding structures, increasing the risk of instability, joint overloading, and pain [20]. Therefore, exercise interventions usually target the lumbar paraspinal muscles specifically [15, 16].

There is mixed evidence as to whether current exercise interventions actually results in morphological changes in the paraspinal muscles (e.g., hypertrophy, reversal of fatty infiltration) and whether paraspinal muscle physiological adaptations will translate in better improvement in patient-related outcomes [21–24]. A recent preliminary study examined the effect of a resistance-based exercise protocol on the cross-sectional area (CSA) and fatty infiltration for both the erector spinae and multifidus muscles [22]. The intervention did not yield any significant morphological change but the investigators suggested further exploration into identifying what types of resistance exercise works best. While another recent study reported decreased in paraspinal muscle fatty infiltration following a 16-week free-weight-based resistance training intervention without isolated lumbar extension exercise [23]. In recent years specific motor control interventions have gained popularity given its focus on retraining control of trunk muscles activation, alignment and movement in order to restore proper function [16]. Motor control exercises often target paraspinal muscles directly however, there is limited evidence on their effectiveness in improving spinal muscle morphology [21, 22].

Previous studies that have used targeted strengthening exercises to improve lumbar muscle strength recommend using exercises that include increased pelvic restraints which limit the activity of other large muscles of the posterior chain (e.g., gluteus and hamstrings) [15, 25]. Since most studies do not include exercises where the pelvis is stabilized it is possible that the lack of morphological changes observed in spinal muscles may be due to the compensation of the other posterior chain muscles [25]. Further studies are needed to examine whether pelvic stabilization during extension exercises is able to effectively target the lumbar extensors and lead to significant morphological and functional changes. Furthermore, we are also aware of only one previous study that has examined the correlation between changes in lumbar muscle morphology with fear avoidance and psychosocial factors [22]. High fear avoidance in patients with chronic LBP is significantly associated with less improvement in disability after 1 year as well as longer sick leave [26]. As such, controlling for factors that could influence the change in disability is crucial.

There is limited evidence linking the physiological and morphological changes in paraspinal muscles with decreases in LBP and self-reported improvements in pain and daily function. Therefore, the primary objective of this study is to compare the effects of combined motor control and isolated lumbar strengthening exercises (MC + ILEX; targeted exercise intervention) versus those of a general exercise group (GE: control intervention) multifidus muscle morphology (e.g. size, fatty infiltration). The secondary aim is to compare the effect of each intervention on overall paraspinal muscle health (morphology and function), and the association of these changes with pain and disability. An exploratory aim is to investigate if psychological factors (e.g., kinesiophobia, catastrophizing, anxiety, depression and sleep) can modify the response to the exercise interventions.

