### Randomization

Participants will be randomly assigned to treatment groups (1:1) using consecutively numbered sealed opaque envelopes (e.g. computer-generated randomization sequence with permuted blocks) created by an individual not involved in the study.

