##### Disability

The Oswestry Disability Index (ODI) will be used to measure participants’ level of self-reported disability in relation to LBP. It is a 10-item scale in which each item is rated from 0 to 5, where 0 means that their pain does not influence that situation and a score of 5 indicates severe disability. The categories included in the questionnaire are pain, walking, lifting, sitting, standing, personal care, sleeping, travel, sex life, and social life. Scores are categorized as minimal, moderate, severe, crippled, or bed bound. The ODI has shown good reliability and validity, and therefore is considered to be the gold standard of measuring disability related to low back pain [50].

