#### Kinesiophobia: Tampa scale of Kinesiophobia (TSK)

The TSK will be used to measure participants’ fear of movement or reinjury in the presence of pain. The TSK-11 contains 11 phrases related to kinesiophobia, such as “I’m afraid I might injure myself if I exercise”, with each rating as a Likert scale from 1 to 4. The scores range between 11 and 44 with increasing scores showing increased levels of kinesiophobia. This tool has been shown to have high reliability and validity [57].

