### Statistical analysis

Descriptive statistics for demographic characteristics and outcomes will be calculated. The pre to post intervention changes in primary and secondary measures will be evaluated with the use of a between-subjects repeated measures ANOVA. Linear mixed models will be used to assess whether baseline psychological scores can modify the response to the exercise therapy treatment. A *p*-value of < 0.05 will be considered statistically significant.

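### The Background calls control of factors affecting change in disability crucial, yet the stated between-arm comparison of disability names no covariate, and baseline psychological scores enter only separate, exploratory modifier models

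*Protocol article*

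**What the plan says.** All references are to the protocol article.

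- **Background, prognostic claim.** The text reports that "High fear avoidance in patients with chronic LBP is significantly associated with less improvement in disability after 1 year", and concludes that "controlling for factors that could influence the change in disability is crucial".
- **Statistical analysis, between-arm comparison.** "The pre to post intervention changes in primary and secondary measures will be evaluated with the use of a between-subjects repeated measures ANOVA". Disability is listed among the secondary outcomes: "The Oswestry Disability Index (ODI) will be used to measure participants’ level of self-reported disability in relation to LBP". The ANOVA is therefore its stated analysis. No covariate is named.
- **Statistical analysis, second model.** "Linear mixed models will be used to assess whether baseline psychological scores can modify the response to the exercise therapy treatment". The model terms and the outcome are not given.
- **Background, status of that second model.** The sentence on this aim opens "An exploratory aim is to investigate if psychological factors" and asks whether they alter the response to exercise.
- **Kinesiophobia subsection, under Possible effect modifiers.** "The TSK will be used to measure participants’ fear of movement or reinjury in the presence of pain". The 11-item form is described.
- **Randomization.** The method is a "computer-generated randomization sequence with permuted blocks". No stratification factor is named.

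**The concern.** The article states a principle for disability and then fixes a comparison that does not apply it. Fear of movement is measured at baseline, but its only stated use is to ask whether the treatment effect differs by score. That is a different question from whether the overall difference between arms has been adjusted for a prognostic factor. Randomisation does not balance the factor by design either, since no stratification is stated.

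In a trial of 50, moderate chance imbalances in a single baseline score are common. If the score predicts change in disability, part of that imbalance passes into the unadjusted estimate, and its interval is wider than it need be. Disability also has no power calculation of its own, because the sample size rests on multifidus cross-sectional area. Precision that needs no new data is therefore worth having. The issue is separate from how baseline ODI is handled; the repeated measures ANOVA already includes baseline ODI as its first time point.

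**Working it through.** **The plan's own figure.** The mean of the four effect sizes in Sample size calculation is (0.87 + 0.90 + 1.00 + 0.81)/4 = 0.895, stated as 0.90. A two-sided t-test at alpha 0.05 with 80% power needs 20.39, so 21 per arm or 42 in total. Then 42 × 1.20 = 50.4, which matches the stated 50 (25 per arm in Procedure). This calculation concerns muscle size, not disability.

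**Inputs.** n = 25 per arm (Procedure). As a low case, n = 20 per arm, from 25 × (1 − 0.20), if both 10% allowances in Sample size calculation are lost to the analysis. The correlation r between baseline fear and change in disability is not given; 0.2 to 0.4 is assumed.

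**Chance imbalance.** The SD of the standardised baseline difference is √(2/n).

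- n = 25: √(2/25) = 0.283; 95% range ±1.96 × 0.283 = ±0.55. The chance of a difference above 0.5 SD is 7.7%.
- n = 20: √(2/20) = 0.316; 95% range ±0.62. The chance of a difference above 0.5 SD is 11.4%.

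**Shift in the unadjusted estimate** at the edge of that range, in SDs of change: r × 1.96 × √(2/n). The smallest case is 0.2 × 0.554 = 0.11; the largest is 0.4 × 0.620 = 0.25.

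**Precision.** Adjustment multiplies the variance of the difference by (1 − r²). Estimating the slope costs a factor of about 1 + 1/(N − 4) under normality: 1 + 1/46 = 1.022 at N = 50 and 1 + 1/36 = 1.028 at N = 40. The equivalent gain in participants is 1/(1 − r²) before that cost, and the same figure divided by 1.022 or 1.028 after it.

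| r (assumed) | 1 − r² | SE ratio √(1 − r²) | Gain before slope cost | Net gain, N = 50 | Net gain, N = 40 |
|---|---|---|---|---|---|
| 0.2 | 0.96 | 0.980 | 4% | 2% | 1% |
| 0.3 | 0.91 | 0.954 | 10% | 8% | 7% |
| 0.4 | 0.84 | 0.917 | 19% | 17% | 16% |

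**Power, for illustration.** With 25 per arm and a true effect of 0.5 SD of change, power is 41% unadjusted, and 42%, 44% and 47% at r = 0.2, 0.3 and 0.4. These figures allow for the lost degree of freedom but not for the slope cost, so they slightly favour adjustment.

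**The case against.** The strongest reply is that this is a short statistical section in a journal article, and that covariates for a secondary outcome usually sit in an analysis plan that is not shown. The sentence in the Background is motivation. It names no model and no instrument, and the article does follow it up by measuring psychological factors and planning models that use them. The cited association is at 1 year, while this trial follows patients for a shorter time. The gain is also small at the low end of the assumed range.

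Much of that stands, and it limits the point. What remains is not a missing detail: the article states the between-arm method for disability, and that method does not take the step the article itself calls crucial. The modifier models do not settle it. A model with score, arm and their interaction would normally include the score's main effect, but the article does not give the terms, does not say that disability is the outcome, and does not make that model the source of the overall comparison. With an interaction present, the arm coefficient depends on the score at which it is read.

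Three stronger readings are tempting, and the documents support none of them:

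- **That the disability comparison is biased or invalid.** Randomisation preserves the type I error of the unadjusted test, and its standard error already reflects chance imbalance. The shift and the loss of precision are two views of the same variance, not two harms.
- **That no baseline psychological score is used anywhere.** The mixed models use such scores; only the between-arm comparison names none.
- **That the Background demands TSK-11, or adjustment of pain.** It mentions neither. It speaks of factors in general, with fear avoidance as the example and disability as the outcome.

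**Conclusion.** The point holds as a mismatch between the Background and the Statistical analysis section on one secondary outcome. The cost is lost precision and exposure to chance imbalance. At 25 and 20 per arm the baseline difference has a chance SD of 0.28 and 0.32, and an imbalance at the edge of its 95% range would move the disability estimate by 0.11 to 0.25 SD. Adjustment would be worth about 1% to 17% more participants net of the slope cost.

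The shift and the gain rest on the assumed r of 0.2 to 0.4, for which the documents offer no figure; near 0.2 the benefit is slight. They also assume that TSK-11, a measure of fear of movement, stands in reasonably for fear avoidance. The primary outcome and the sample size of 50 are unaffected.

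**What to change.** In the Statistical analysis section, pre-specify baseline TSK-11 as a covariate in the between-arm model for disability, before any unblinded look at the data, so that the covariate cannot be chosen on the results. In a repeated measures model the score should enter together with its interaction with time. With complete data, a main effect alone leaves the arm-by-time contrast, and so the comparison of change, as it was.

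Report the unadjusted result alongside. Keep the modifier models separate and labelled exploratory. If the analysis plan already contains such a covariate, the article needs only a sentence saying so.

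The score is already collected, so the cost is one degree of freedom for each change contrast, for example from 48 to 47 with 50 participants. Applying the same adjustment to pain is optional and does not follow from the Background.

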## Methods/design

### Study design

The proposed study is a two-arm prospective randomized controlled trial (RCT), with test-retest design (Fig. 1). This protocol was reported in accordance with the SPIRIT guidelines [27] and CERT recommendation for Exercise Interventional Trials [28].

**Fig. 1 Fig1:**
[figure not shown]
Consort flow diagram

### Study setting

This study will be conducted at the PERFORM Centre, Concordia University (registration trial NTCT04257253). The proposed project was approved by the Central Ethics Research Committee of the Quebec Minister of Health and Social Services (# CCER-19-20-09). All participants will sign a consent form prior to entering the study.

### Participant recruitment

Participants will be recruited by clinicians in local orthopaedic clinics working in Montreal, Canada and from the local university community by email advertising. Clinicians will assess the participant for eligibility and send referral to the research team, which will confirm eligibility. Similarly, a member of the research team will interview individuals who respond to the advertisement to confirm eligibility.

### Participants

#### Inclusion criteria

Participants must meet all of the following criteria for inclusion:
Chronic, non-specific low back pain (LBP) for a minimum of 3 months (with or without leg pain)Aged between 18 and 65 years oldSpeak either French or EnglishCurrently seeking care for LBPScore either “moderate” or “severe” on the modified Oswestry Low Back Pain QuestionnaireDo not engage in any sport or fitness training specifically for the lower back muscles up to 3 months before the start of the trial

#### Exclusion criteria

Participants will be excluded if they meet one of the following criteria:
Any evidence of nerve root compression or reflex motor sign deficits.Previous spinal surgery or vertebral fractures.Major lumbar spine structural abnormalities (e.g., spondylosis, spondylolisthesis, scoliosis > 10°)PregnancyHealth conditions that prevent the safe participation in physical exercise as determined by the Physical Activity Readiness Questionnaire.

### Randomization

Participants will be randomly assigned to treatment groups (1:1) using consecutively numbered sealed opaque envelopes (e.g. computer-generated randomization sequence with permuted blocks) created by an individual not involved in the study.

### Blinding

Only the assessor will be blinded, as blinding of therapists and participants is generally not possible in exercise intervention trials [29].

### Procedure

All research activities will take place at the PERFORM Centre, Concordia University. This centre houses 8000m^2^ of laboratories, assessment suites, and lifestyle intervention space, all designed specifically to foster interdisciplinary environment devoted to health prevention research. The infrastructure has all the necessary research platforms (e.g., Imaging Suite, Conditioning floor and Functional Assessment suite) for the conduction of the proposed RCT.

Eligible participants will be randomized between the GE (*n* = 25) and MC + ILEX (n = 25) groups. The participants of the two groups will undergo a 12-week intervention programme with two individually supervised exercise sessions per week of approximately 45 min. The treatment will be provided by a certified athletic therapist (MC + ILEX) with 2 y of clinical experience or graduate exercise science master’s student (GE). Participants in both groups will be advised to complete a home exercise programme during the intervention and after discharge. During the intervention period, participants will be asked to refrain from receiving other types of treatment (e.g., chiropractor, osteopath, massage) and medication, although this will not hinder participation. Participants will be asked to report any co-interventions.

### General exercise group (GE)

The GE participants will engage in a program that will include a 10-min aerobic warm-up (incline treadmill walking or stationary bike), resistance training exercises, followed by trunk-leg stretches. The machine-based resistance training program will be divided into a 2-day split (non-consecutive days) with different muscle group focuses for each day (Table 1). Three sets will be performed for each exercise. The difficulty of the intervention will be progressively increased over the course of the 12-week intervention based on a study procedure developed by Iversen et al. [30] with the following target repetitions: week 1–2, 15–20 repetitions; week 3–5, 12–15 repetitions, week 6–8, 10–12 repetitions; week 9–12, 8–10 repetitions. The weights will be increased by 5% as soon as the participants are able to complete 2 more repetitions than the amount assigned for that period. Stretching exercises will be performed at the end of each session (e.g., cat cow, pigeon, deep lunge, piriformis stretch) and each position will be held for 10 s, 3 times on each side in accordance with ACSM guidelines. As most patients with LBP sedentary lifestyles due to the nature of their pain, the overall goal of this intervention is to return patients to the normal activities of daily living (e.g., rising, bending, lifting, walking) by enhancing lower-body strength and flexibility. Such general exercise programs have been found to reduce pain and improve function (e.g., moderate level of evidence) [31].

**Table 1 Tab1:** Two-day split exercise program performed by the GE group

Day 1	Day 2
Hip extension (multi-hip machine)*	Goblet Squat
Prone Leg Curl*	Step up
Lat pull down*	Leg extension*
Seated row*	Peck deck*
Hip Abduction*	Lying side hip raises
Hip Abbuction*	Abdominal curl

*Exercise performed on a resistance machine

